A recent randomized clinical trial (RCT) (IREM) found promising results for two treatments for Ch-PTSD, namely imagery rescripting (ImRs) and EMDR [11]. ImRs involves the patient recalling the start of the traumatic experience and, subsequently, imagining an intervention that changes the course of events to a more positive outcome aimed at satisfying the needs of the patient [12, 13]. In EMDR, the therapist instructs the patient to focus on a traumatic memory, composed of images, emotions, cognitions, and physical sensations, while the therapist concurrently provides a form of active distraction (e.g., following the back and forth movements of the finger of the therapist) [14]. There are indications that both treatments are effective treatments for patients with PTSD related to childhood trauma. In a meta-analysis on treatments for Ch-PTSD, three RCTs evaluating the effectiveness of EMDR were included [7]. It was found that EMDR was effective in treating PTSD as a consequence of childhood trauma, yielding moderate to high effect sizes. Although ImRs has been less studied to date [15], a recent RCT into the effectiveness of ImRs as a stand-alone treatment for Ch-PTSD concluded that ImRs was effective and highly acceptable [16]. Moreover, in the IREM trial evaluating the comparative effectiveness of EMDR and ImRs, large treatment effects were found for both treatments between baseline and one-year follow-up (i.e., *g* = 2.24 for ImRs and *g* = 1.86 for EMDR on the Clinician Administered PTSD Scale for DSM-5) and treatment dropout was limited to 7.7%. These results were favorable compared to the results found in a meta-analysis on treatments for Ch-PTSD [7]. This meta-analysis found an average effect size for pre-treatment to long-term follow-up (≥ 6 months) of *g* = 1.56 and an average dropout of 22.3%. In discussing the positive outcomes of the treatments in the IREM trial, the authors proposed that the low dropout rate and large symptom reduction might be related to the twice-weekly session frequency of each treatment condition. In contrast, in routine mental health care, trauma-focused treatments are commonly delivered once a week [17]. More insight into the impact of session frequency on treatment outcome is therefore needed.

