#### Secondary objectives

The IREM-Freq study has several secondary objectives. These include investigating (1) the comparative effectiveness of EMDR and ImRs, (2) whether treatment type (i.e., EMDR versus ImRs) moderates the effect of session frequency, (3) the hypothesized change mechanisms underlying the effects of session frequency on treatment outcome (i.e., memory and learning, therapeutic alliance, motivation, and reluctance and avoidance), (4) the (differential) change mechanisms of EMDR and ImRs, (5) potential predictors of treatment outcome and PTSD severity, (6) the role of emotions, cognitions, and memory in the change in PTSD symptoms, (7) the impact of trauma-focused treatments on learned helplessness, (8) the optimization of treatment selection through identifying patient characteristics that predict treatment response across treatment types (EMDR and ImRs) and treatment frequencies (twice-weekly and once-weekly sessions), (9) the perspectives of patients and therapists on the treatments, (10) the network structure of PTSD symptoms, and (11) sudden treatment gains.

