## Methods/design

### Design

The study is an international, multicenter superiority RCT with a two by two factorial design, with an equal allocation ratio. The first factor is treatment frequency (twice a week versus once a week), and the second factor is the treatment type (EMDR versus ImRs). The study is registered at the Netherlands Trial Register, part of the Dutch Cochrane Center, with registration number NL6965, and complies with the World Health Organization Trial Registration Data Set. Modifications to the protocol will require a formal amendment to the protocol. The amendments will be examined by the ethics committees of each country and, if approved, included in the trial registration. This trial adheres to the SPIRIT guidelines and methodology [39], see Additional file 1: Appendix A for the SPIRIT checklist. For an overview of the study design, including the recruitment, randomization, assessments, and treatments, see Fig. 1.

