### Sample size

We aim to include 220 participants with about an equal number of participants (*n* = ± 55) in each of the four conditions (i.e., EMDR once a week, EMDR twice a week, ImRs once a week, and ImRs twice a week). We expect a dropout percentage of 10%, which is a conservative estimate given the 7.7% dropout found in the IREM study, the predecessor of the current study [11]. Each site intends to recruit at least 20 patients.

A sample size of *N* = 200 is sufficient to have 94% power to detect a medium effect size (i.e., Cohen’s *d* = .50) between frequency groups (i.e., twice-weekly versus once-weekly sessions of EMDR and ImRs) at post-test or follow-up, assuming equal sample sizes and a two-tailed significance level of *p* < .05, and based on a *t*-test. In addition, the study has 80% power to detect a group difference with an effect size of Cohen’s *d* = .40. Moreover, in case of a significant treatment by frequency interaction, with *N* = 200 power is 80% to detect an effect size of *d* = 0.57 for a comparison of frequency effects within a treatment at a two-tailed significance level of .05 (*t*-test at post-test or follow-up, assuming equal sample sizes of 50 per frequency).

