### Statistical analyses

The statistical analyses will be performed according to the intention-to-treat principle. Change in the primary and secondary outcome measures and the relative effectiveness of the two frequency conditions (twice-weekly frequency condition versus once-weekly frequency condition) will be analyzed using mixed regression analyses. By using mixed regression analysis, all available data will be used, and dependencies among observations nested within individuals will be taken into account. Appropriate forms of the mixed regression models will be selected, based on the variable type (e.g., scale, count, dichotomous) and taking into account the distribution of the residuals. To assess the comparative effectiveness of EMDR and ImRs and whether treatment type moderates the effect of session frequency, additional terms will be added to the model. In addition to the primary analyses based on the intention-to-treat principle, a completers analysis focused on the change in the primary outcome measure will be conducted by excluding patients who discontinued treatment or deviated from the protocol (e.g., duration of more than 16 weeks in the once-weekly frequency condition, other psychological treatment next to the study treatment, unstable level of medication during the treatment period). No interim analyses are planned. Finally, to examine underlying change mechanisms of session frequency (i.e., memory and learning, therapeutic alliance, motivation, and reluctance and avoidance), advanced mediation analysis will be performed (e.g., mixed regression for Granger Causality models [118]).

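### The primary frequency model appears to leave out treatment type, the second randomised factor; including it from the start is a small, free gain in precision

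*Protocol article*

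**What the plan says.** The Design section of the protocol article describes a "multicenter superiority RCT with a two by two factorial design, with an equal allocation ratio", and names the factors: "The first factor is treatment frequency (twice a week versus once a week), and the second factor is the treatment type". Under Allocation, patients are randomised to all four cells in blocks of four or eight, per center and stratified by gender, so type and frequency are close to orthogonal by construction.

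The frequency comparison is the primary objective. EMDR versus ImRs, and moderation of the frequency effect by type, are the first two secondary objectives.

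The Statistical analyses section says that "the relative effectiveness of the two frequency conditions (twice-weekly frequency condition versus once-weekly frequency condition) will be analyzed using mixed regression analyses". For the two treatment-type questions, including "whether treatment type moderates the effect of session frequency, additional terms will be added to the model". No list of fixed effects is given. The Sample size section bases power on an unadjusted two-group t-test that pools over treatment type.

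**The concern.** If type terms are added to the model in order to answer the secondary questions, the model before that addition does not contain them, and that is the model for the primary question. Treatment type is a randomised design factor, not an optional covariate. If EMDR and ImRs differ in mean change, leaving type out moves that difference into the residual variance and widens the reported interval for the frequency effect.

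The sequence also produces at least two models, each with its own frequency coefficient. If type is coded 0/1 and the interaction is added, the frequency coefficient becomes the effect within one treatment and no longer the average over both. The primary hypothesis concerns both treatments, so the average is the natural target. What is at stake is a little precision and clarity about which coefficient is primary. The validity of the test is not at stake.

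**Working it through.** **Inputs**
- N = 200 analysed, 100 per frequency; d = 0.50 and d = 0.40; two-sided alpha 0.05; t-test (Sample size).
- Four equal cells (Design, Allocation).
- Size of the type effect: not stated for this trial. The Background gives predecessor within-group effects, baseline to one-year follow-up, of g = 2.24 (ImRs) and 1.86 (EMDR). Their gap, 2.24 - 1.86 = 0.38, is used as an **assumed** between-type difference d_t in within-cell SDs, with range 0 to 0.5.

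**Step 1. Reproduce the stated power.** Noncentral t with noncentrality d x sqrt(n/2), n per group:
- d = 0.50, n = 100: 0.50 x sqrt(50) = 3.536, power 94.0% (stated 94%).
- d = 0.40, n = 100: 0.40 x sqrt(50) = 2.828, power 80.4% (stated 80%).
- d = 0.57, n = 50: 0.57 x sqrt(25) = 2.850, power 80.6% (stated 80%).

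All three reproduce.

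**Step 2. Residual variance when type is omitted.** With two equal halves whose means differ by d_t, the variance between them is d_t²/4. Relative to the within-cell variance, the residual is multiplied by f = 1 + d_t²/4. At d_t = 0.38, f = 1 + 0.1444/4 = 1.0361. Hence:
- share of variance explained by type: 0.0361/1.0361 = 3.5%;
- standard error ratio: sqrt(1.0361) = 1.018, or 1.8% wider;
- patients needed to make up the loss: 200 x 1.0361 = 207.2, about 7 more.

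**Step 3. Power at d = 0.40.** The plan's d comes from an unadjusted comparison, so it is read here as scaled to the SD pooled over types. Adding type then raises the noncentrality by sqrt(f): 2.828 x 1.018 = 2.879, power 81.7%.

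| Assumed d_t | f | SE wider by | Equivalent N | Power without type | Power with type |
|---|---|---|---|---|---|
| 0 | 1.0000 | 0% | 200 | 80.4% | 80.4% |
| 0.2 | 1.0100 | 0.5% | 202 | 80.4% | 80.7% |
| 0.38 | 1.0361 | 1.8% | 207 | 80.4% | 81.7% |
| 0.5 | 1.0625 | 3.1% | 212.5 | 80.4% | 82.7% |

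If d is instead scaled to the within-cell SD, the comparison at d_t = 0.38 is 79.0% without type against 80.4% with it. At d = 0.50 it is 93.3% against 94.0%.

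**Step 4. Simulation.** In 20,000 exactly balanced trials with d_t = 0.38 and d in within-cell SDs, power was 79.8% without type and 80.8% with it at d = 0.40, and 93.7% and 94.1% at d = 0.50. With no frequency effect, the rejection rate was 4.7% without type and 5.1% with it. The gap at d = 0.40 is slightly smaller than in the formula because exact balance already protects the estimate itself; omission inflates only its reported standard error.

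**Step 5. Sensitivity.** Baseline adjustment would shrink the residual and make type a larger share of it. With an assumed baseline correlation of 0.5, residual variance falls to 1 - 0.25 = 0.75, the inflation becomes 0.0361/0.75 = 4.8%, and the standard error is sqrt(1.048) = 1.024 times as large. It remains a small effect.

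**The case against.** The strongest reply is that the omission is inferred. The article lists no fixed effects and nowhere says that type is excluded. A condensed article commonly leaves the exact model terms to a full protocol or analysis plan, neither of which is shown. That stands as a limit on certainty. It does not remove the point, because the article does state a modelling sequence, and as worded that sequence brings type in for the secondary questions.

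The size is also open to challenge. Subtracting two within-group g values is not a between-treatment effect size. The values refer to one-year follow-up, whereas the primary outcome here is the change to 24 weeks. The Background reports large effects for both treatments and no test of a difference. This stands too, which is why 0.38 is only an assumption and the range includes zero.

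A reader might be tempted by stronger conclusions that the documents do not support:
- *That the frequency estimate is biased or departs from the factorial design.* In a balanced 2x2 the frequency contrast pooled over type already is the factorial main effect, and adding a type main effect leaves the point estimate essentially unchanged.
- *That the stated power is too high.* It reproduces, and it comes from an unadjusted comparison that takes no credit for including type.
- *That the type I error is inflated.* If anything, the test without type is slightly conservative.
- *That precision is certainly lost.* It is lost only if the types differ in mean change.

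**Conclusion.** The point holds as a minor matter of efficiency and clarity. On the natural reading of the Statistical analyses section, the primary frequency effect is estimated without the second randomised factor. The cost is about 1.8% on the standard error and about one point of power at d = 0.40, if the between-type difference is 0.38. Over the assumed range of 0 to 0.5, the cost runs from nothing to 3.1% on the standard error and 2.3 points of power (82.7% - 80.4%). These figures rest on balanced cells, a common within-cell variance, and an assumed type effect that the document does not supply. Neither the validity of the primary test nor the sample size is affected.

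**What to change.** State in the Statistical analyses section that the primary model contains session frequency and treatment type, each with its terms for time, from the start. Code type -0.5/+0.5 so that the frequency coefficient is the effect averaged over EMDR and ImRs, and remains so when the interaction is added. For the moderation question, add only the frequency-by-type terms. The EMDR versus ImRs comparison can then be read from the same primary model.

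The cost is one sentence and one or two degrees of freedom. Sample size, randomisation and data collection are unchanged. If a full analysis plan already specifies this model, the article's wording only needs to be aligned with it.

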### Eligibility criteria

Patients are eligible if they (1) are between 18 and 70 years old; (2) have a primary diagnosis of PTSD as assessed by the Structural Clinical Interview for DSM-5-Clinician Version or Research Version (SCID-5-CV/RV); (3) have experienced the worst traumatic event (defined according to the DSM-5) before the age of 16 and agree that this trauma will be the focus of treatment; (4) have been experiencing PTSD symptoms for longer than 3 months; and (5) have an adequate proficiency in the language of the center or an adequate proficiency in the English language in case the center has English-speaking research assistants and therapists. Patients will be excluded if they (1) have experienced a trauma less than 6 months ago; (2) meet criteria for a current substance use disorder with a moderate or severe severity level (i.e., more than four symptoms), diagnosed with the SCID-5-CV/RV (after 6 weeks of abstinence, participation is possible); (3) fulfill the criteria of a psychotic disorder, diagnosed with the SCID-5-CV/RV; (4) have been diagnosed with the SCID-5-CV/RV with bipolar I disorder; (5) have acute suicide risk; (6) have an IQ below 80; (7) experience serious neurological problems (e.g., dementia); (8) are scheduled to start another form of PTSD treatment; (9) have received PTSD focused treatment within the past 3 months; (10) use benzodiazepine (after 3 weeks of abstinence, participation is possible); or (11) are not able to attend the treatment sessions of both randomization possibilities (i.e., 12 sessions of 90 min within 8 weeks and 12 sessions of 90 min within 16 weeks). In addition, patients will not start treatment unless their medication use has been stable for at least 3 weeks. Finally, patients are not allowed to start any form of psychological treatment or medication between the screening period and 24 weeks after the start of the study treatment (non-PTSD focused supportive treatment may be continued during the screening and waitlist period).

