The additional substudies will be analyzed using different statistical methods. To study (differential) mechanisms of change of EMDR and ImRs (i.e., the strength of the encapsulated belief, and the vividness and valence of the traumatic memory of the index trauma), mediation analysis will be conducted using Granger Causality models. In addition, mixed regression analysis will be used to investigate whether comorbid personality disorder psychopathology and trauma characteristics are related to treatment effects. The role of emotions, cognitions, memory, and learned helplessness in altering PTSD symptoms over time will be examined using advanced mediation analyses (e.g., mixed regression for Granger Causality models [118]). Furthermore, a two-step approach will be used to determine the optimal treatment type (EMDR versus ImRs) and frequency (twice-weekly versus once-weekly) for a particular patient. First, we will examine which of the candidate predictors predict what treatment and which frequency will be more beneficial. Different variable selection approaches can be applied, including bootstrapping procedures [119], a Random Forest machine learning approach [120], and the domain approach outlined by Fournier et al. [121]. Second, a prediction model will be built based on the identified predictors to generate individual treatment recommendations geared to predict the primary outcome measure (i.e., PTSD severity). Since statistical methods for the selection of variables and generating individual treatment recommendations are still in development, we will select the optimal methods at the time of the analyses. Finally, to investigate the network structure of (complex) PTSD symptoms at baseline and changes in the network structure of patients as a consequence of treatment, network analysis and longitudinal comparisons between networks will be conducted (e.g., [122, 123]).

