#### Network models of PTSD symptoms

The network approach is an alternative approach to conceptualize mental disorders [141]. Network analysis will, therefore, be performed to gain more insight into the network structure of (complex) PTSD symptoms. More specifically, this study aims to investigate the cross-sectional structure of (complex) PTSD symptoms (e.g., connectivity, centrality) of patients before the start of the treatment [142], as well as its change during the course of treatment [143].

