A final strength of this study is the methodological quality. According to Ehring et al. [7], studies on the effectiveness of treatments for Ch-PTSD often lack methodological quality and more rigorous approaches are needed. This trial includes a multi-method assessment approach (i.e., self-report measures and semi-structured interviews), an assessment of treatment integrity, manualized treatments, and a long-term follow-up. Moreover, the semi-structured interviews are administered by independent, trained research assistants to control for interviewer bias. In addition, the outcome and presumed mechanisms of change of session frequency are assessed every treatment session, allowing us to examine concurrent as well as temporal relationships using state-of-the-art statistical analysis methods [152].

There are several limitations to this study that should be considered when evaluating the results. First, the study treatments are not compared to other trauma-focused treatments, including TF-CBT approaches such as imaginal/prolonged exposure (IE/PE) and cognitive (processing) therapy (CT/CPT) for PTSD. In addition, this study does not include a randomized waitlist control group, which can affect internal validity. When patients improve in all treatment conditions and there are no differences between conditions, it cannot be ruled out that non-treatment-specific factors (e.g., attention, time) have caused the improvements. On the other hand, the study does include an additional assessment if there is a waitlist period of at least 5 weeks (i.e., waitlist assessment). If there are enough patients with a waitlist assessment, we will test the effects of active treatment compared to naturalistic waitlist, assuming that the duration of the waitlist period is nonbiased. Moreover, including a control group receiving no treatment above the natural wait at the participating site would increase patients’ resistance to participate in the trial, which would result in selection bias.

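### Before-to-after change in the symptom network is read as an effect of treatment, but a wider spread of severity after treatment can produce such change with an unchanged structure, and no randomised untreated arm can separate the two

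*Protocol article*

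**What the plan says.** The Statistical analyses section describes the network substudy as a study of the baseline structure of (complex) PTSD symptoms and of "changes in the network structure of patients as a consequence of treatment, network analysis and longitudinal comparisons between networks will be conducted". The section on network models of PTSD symptoms describes the pre-treatment network, with connectivity and centrality as examples, "as well as its change during the course of treatment". This is item 10 in the list of secondary objectives. No contrast of networks between arms is mentioned.

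Four other places bear on it:

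- Eligibility criteria: patients must "have a primary diagnosis of PTSD as assessed by the Structural Clinical Interview for DSM-5-Clinician Version or Research Version". No minimum severity score is set beyond the diagnosis.
- Design and Allocation: all four conditions are active treatment.
- Prediction of (differential) treatment response: patients are said to differ substantially in how they respond.
- Discussion, limitations: "this study does not include a randomized waitlist control group, which can affect internal validity". If all conditions improve alike, "it cannot be ruled out that non-treatment-specific factors (e.g., attention, time) have caused the improvements". A comparison with a naturalistic waitlist is foreseen if enough patients have a waitlist assessment.

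**The concern.** A correlation between two symptoms depends on how the symptoms relate to each other and also on how widely overall severity varies in the sample. Selecting everyone on a diagnosis tends to narrow that variation at baseline. After treatment some patients have recovered and others have not, so it tends to widen. All inter-symptom correlations can then rise together although no relation between symptoms has changed.

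A before-to-after comparison does not distinguish this from a change in structure. Without a randomised untreated arm it also cannot separate treatment from ordinary individual fluctuation, which widens the spread in the same way. The Discussion's caveat is about mean improvement and does not reach this problem. At stake is a published statement that treatment altered the network, when only the distribution of severity may have moved.

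**Working it through.** **The plan's own figure.** There is none for networks. The Sample size section concerns the frequency comparison on PTSD severity and does not bear on this point.

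**Inputs from the protocol.** The PCL-5 gives 20 items scored 0-4; the article does not name the network instrument. The power calculation uses N = 200. Baseline-to-one-year effects in the predecessor trial were g = 1.86 and 2.24.

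**Assumed inputs.** One severity factor with the same loading (0.65) before and after; entry by a noisy diagnostic screen of reliability 0.7; a mean fall of 1.5 latent SD; individual change with SD s, independent of baseline severity. If more severe patients improved systematically more, the spread would widen less.

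**Step 1, approximation by hand.** With loading λ and severity variance V, the correlation between two items is r = λ²V / (λ²V + 1 − λ²). Here λ² = 0.4225 and 1 − λ² = 0.5775.

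- The simulated baseline value r = 0.235 corresponds to V = 0.235 × 0.5775 / (0.4225 × 0.765) = 0.42.
- s = 0: V stays at 0.42 and r at 0.235.
- s = 0.5: V = 0.42 + 0.25 = 0.67, r = 0.283 / (0.283 + 0.5775) = 0.33.
- s = 0.8: V = 0.42 + 0.64 = 1.06, r = 0.448 / (0.448 + 0.5775) = 0.44.

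The mean fall does not appear in the formula. Only the spread matters.

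**Step 2, simulation with items scored 0-4.** Baseline mean correlation is 0.235. After the 1.5 SD fall it is 0.239 (s = 0), 0.32 (s = 0.5) and 0.41 (s = 0.8), slightly below the hand values because the items are coarse. These are ratios of 0.32/0.235 = 1.36 and 0.41/0.235 = 1.74 for the last two. With no mean improvement and s = 0.5, a parallel run gives 0.23 to 0.31.

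**Step 3, partial correlations.** In a parallel run, the sum of absolute partial correlations goes from 8.51 to 8.96 (s = 0.5) and 9.27 (s = 0.8): 8.96/8.51 = 1.05 and 9.27/8.51 = 1.09. The direction is the same, and the movement is much smaller.

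**Step 4, a second model.** Here the loading is 0.6 and selection is by a DSM-type symptom count on the same items. At a fall of about 1.8 baseline SD, with s = 0, 0.5 and 1:

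- the total-score SD goes from 11.1 to 11.0, 12.4 and 15.7;
- the mean correlation goes from 0.226 to 0.250, 0.309 and 0.439.

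At a fall of about 3.5 SD with uniform response it drops, from 0.226 to 0.198, because most scores lie near the floor.

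**Step 5, what a test would report.** With N = 200 and unchanged structure, a paired bootstrap of the mean correlation declared the later network stronger in 13%, 68%, 97% and 100% of simulated trials for s = 0, 0.3, 0.5 and 0.8. A separate run gave 91% at s = 0.5 and 100% at s = 0.8. No test on a partial-correlation network was run.

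**Step 6, the randomised alternative.** Two random groups of 100 compared at the same follow-up, with the same structure and spread, differed in 4-6% of trials. If the arms differ in spread (s = 0.5 against 0.8), the mean correlations are 0.31 and 0.40 with identical structure. This contrast therefore needs the same check.

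**The case against.** Five points weigh on the other side.

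- **Cause.** A reader might infer that selection at entry makes the later network look stronger by itself. The documents do not support that. With uniform response the rise is 0.235 to 0.239, and most of the larger figures come from variation in individual change. Where that variation is a differential response to treatment, the wider spread is itself an effect of treatment. Selection alone had a large effect only under an added minimum total score of 40 on the analysed items (0.12 to 0.18 with uniform response), and the protocol sets no such cut. This objection stands, and the point is limited accordingly. A treatment effect on spread is still not a treatment effect on structure.
- **Method.** The article names no estimator. The PCL-5 is completed before each session from session 2, so session-level networks are possible. This stands for the size of the problem. The causal wording remains whichever estimator is used.
- **Waitlist.** The Discussion foresees a naturalistic waitlist comparison, which would give a second pre-treatment measurement. It is relevant, but it is conditional on numbers, not randomised and not linked to the network aim.
- **Remedy.** Contrasts between arms can also be distorted by unequal spread. This stands and is met in the fix.
- **Weight.** This is one of eleven secondary objectives, without a directional hypothesis. That also stands.

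**Conclusion.** The point holds in a limited form. The planned before-to-after comparison cannot by itself show that treatment changed the structure of the symptom network, because a change in severity spread gives the same signal with or without mean improvement.

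The size is not derivable from the protocol. Under the stated assumptions the mean correlation rises from about 0.24 to 0.32-0.41 for response SD 0.5-0.8. It is almost nil for uniform response, smaller for partial correlations and possibly reversed at the floor. A reader might also infer that the network is bound to look stronger, or that any reported change would be spurious. Neither follows: strengthening is an expectation that depends on how variable response turns out to be, and a real change in structure may coexist with it.

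The correction is worth making because the wording fixes a causal reading in advance and is cheap to change. It concerns a substudy only.

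**What to change.** 1. In Statistical analyses, replace the wording that makes treatment the cause with a descriptive statement of change in the network from before to after treatment.
2. Report item variances and total-score variance at each assessment used for a network.
3. Judge the observed change against a null simulated with unchanged structure and the observed shift in the mean and spread of severity.
4. Rest any causal statement on the randomised contrasts, twice-weekly against once-weekly and EMDR against ImRs, at the same assessment. Apply the same check on spread, since arms may differ in it.

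The cost is a change of wording and some computing. The contrast between arms has about 100 patients per network (200/2), so it is less precise. It also answers a narrower question: the effect of one treatment format relative to another, not the effect of treatment as such.
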